### Data analysis

Thematic analysis will be conducted since it has been widely used in exploratory qualitative studies. Thematic analysis is about identifying of emergent themes through inductive coding informed by theory (TFA) while allowing surprising findings and identification of phenomena not initially expected.

The procedure for data analysis will involve: organizing data, applying codes to textual excerpts that either are consistent with predetermined themes or suggest new emergent categories of phenomena, "testing" emergent understandings of data as analyses proceed, exploring alternative explanations of data (including counter-evidence and inconsistencies), and writing up results.

### Sub-study Two: Quantitative study

The purpose of this quantitative sub-study is to measure feasibility (actual fit, suitability for everyday use and practicability) and preliminary effectiveness of ACT-DNA-v to address psychosocial/mental health barriers to adherence (depression, anxiety & stigma).

### Sub-study design.

An open label randomized controlled study will be used to achieve the sub-study objectives. The design will involve randomly allocating ALWHA's to either the intervention or control group. The intervention group will be exposed to the adapted mindfulness and acceptance-based intervention while the control group will receive standard of care (ART related counselling). At

baseline, data on proximal psychosocial barriers to adherence (depression, anxiety, stigma) and process factors (psychological flexibility) will be collected.

#### *Randomization*

Participants will be randomly allocated to the intervention or control group using computer-generated random numbers. A block size of six with equal individuals going to the two arms per block will be considered sufficient to obtain individuals allocated in a ratio of 1:1 in terms of intervention to the control groups.

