#### *Allocation concealment*

The sequence will be concealed using sealed serialized brown opaque envelopes that will be kept by the independent statistician who is not part of the study.

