#### *Allocation implementation*

Trained research assistants will pick the envelopes in consecutive ascending order and allocate the participants to the different arms upon opening the envelope.

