#### *Blinding:*

This will be an open-label randomized study because the staff will be involved in the care of the participants, assessment of the outcome and the nature of the psychosocial interventions to be administered.

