##### *Inclusion Criteria:*

Participant should be 15-19 years of age, diagnosed HIV positive, attending care at Kisenyi Kitebi health center for the last 6 months, on first or second line of treatment, can speak/understand

Luganda or English and willing to provide informed consent/assent. All records will be confirmed via clinic medical charts.

*Exclusion criteria:*

A participant will not be eligible to be part of the study if he/she plans to move out of the catchment area within six months, or if he/she is participating in another study related to HIV and care improvement.

*Sampling for sub-study two*

*Sample size*

The following assumptions are considered for determining the appropriate sample size for the quantitative study.

Assumptions:

$$N = 2 \frac{[Z\alpha + Z\beta]^2 S^2}{(\mu_1 - \mu_2)^2}$$

where:

$Z\alpha$  is standard normal value corresponding to level of significance

$Z\beta$  is standard normal value corresponding to power of the study

$\alpha$ =acceptable type 1 error

$\beta$ = type II error

$\mu_1$  is mean in control group and  $\mu_2$  is mean intervention

$\mu_1 - \mu_2$  =effect size (minimum meaningful difference between the means in the control and intervention groups)

$S$ =standard deviation of the outcome in the control group

$N$  is the sample size per group

$Z\alpha = 1.96$ ,  $Z\beta = 0.84$ ,  $\alpha = 0.05$  in 2 tails,  $\beta = 0.20$  (at 80% power).

Considering a study evaluating effectiveness of Acceptance and Commitment Therapy (ACT) on reducing the depressive symptomatology among Swedish and Australian adolescents (Livheim et.al, 2015), the difference in means of the post treatment RADS2 scores between the ACT arm and control arm was 4.09 while the standard deviation in the control arm was 5.13.

Substituting into the formula,

$$N = (2(1.96 + 0.84)^2 \times 5.13^2) / (4.09^2)$$

$$N = 25.1$$

N=26 participants in each group

If we consider a possible clustering in any of the two sites and a design effect of 2.0, the new minimum sample size is  $26 \times (2) = 52$ . If we consider a 10% loss to follow-up, the revised sample size will become  $(52 \times (1 / (1 - 0.10))) = 58$  participants. We, therefore, aim to recruit, **a total of 116 participants** at 80% power of detecting a mean difference of 4.09 or more in the intervention.

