#### Sampling method

To obtain participants for the Quantitative study, convenience sampling will be used at the screening stage, adolescents will be approached for potential enrollment into the study. Only those who consent/assent will be enrolled. Consent from guardians will also be sought for participants below the age of 18.

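### A single fixed block of six in an open-label trial lets anyone who knows the block size and has seen all earlier allocations foresee up to about a quarter of assignments

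*Protocol*

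**What the plan says.** Under Randomization, the protocol uses computer-generated random numbers and fixes one block length: "A block size of six with equal individuals going to the two arms per block will be considered sufficient". The aim is "individuals allocated in a ratio of 1:1 in terms of intervention to the control groups", so each block holds three participants per arm. No other or varying block size is mentioned.

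Allocation concealment relies on "sealed serialized brown opaque envelopes that will be kept by the independent statistician who is not part of the study". Allocation implementation then says: "Trained research assistants will pick the envelopes in consecutive ascending order and allocate the participants to the different arms upon opening the envelope".

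The Sub-study design section states that "An open label randomized controlled study will be used to achieve the sub-study objectives". The Blinding section gives the reason: "This will be an open-label randomized study because the staff will be involved in the care of the participants, assessment of the outcome".

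On entry to the trial, the Sampling method section says that "convenience sampling will be used at the screening stage, adolescents will be approached for potential enrollment into the study". The target under Sample size is "a total of 116 participants", from a study population put at roughly 480.

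The protocol does not say whether there is one list or one per clinic, who approaches the adolescents, whether those people know the block size, or whether consent and baseline assessment must be complete before an envelope is opened.

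**The concern.** Sealed opaque envelopes hide the next slip. They do not hide what follows from the slips already opened. In an open-label trial past allocations are visible, and serial numbers show where each block of six begins and ends. Once one arm has used its three places in a block, the rest of that block is known, and the sixth place is always known.

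Foreknowledge matters only if it can affect who is approached or enrolled, and when. The protocol leaves room for this. Approach is by convenience, and about one in four of the available adolescents is needed (116/480 = 24%). Recruitment is planned within one month, so a running tally is easy to keep.

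If more motivated adolescents were held back for an expected intervention place, two results could be flattered. One is the questionnaire scores for depression, anxiety and stigma. The other is the feasibility measures, which depend on retention and session completion.

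**Working it through.** **Inputs**
- Block size 6, three per arm, 1:1 (protocol, Randomization).
- Total of 116 (protocol, Sample size).
- Share of participants per clinic: not given. Study Setting puts about 590 adolescents in care at Kisenyi and 400 at Kitebi, so 590/990 = 60% at the larger. These counts are not limited to ages 15 to 19. A share of 50% to 60% is therefore an assumption.

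**The plan's own figure.** The protocol states no predictability figure, so the base is 116. From its 26 per group: 26 × 2.0 = 52; 52/(1 − 0.10) = 57.8, rounded up to 58; 58 × 2 = 116. This reproduces. (The formula itself gives 2 × 2.80² × 5.13²/4.09² = 24.67 rather than the stated 25.1. That has no bearing here.)

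**Certain allocations per block.** There are C(6,3) = 20 equally likely orderings. An allocation is certain when one arm already has its three.
- Positions 1 to 3: 0.
- Position 4: the first three are all in one arm, 2/20 = 1/10.
- Position 5: the first four split 3 to 1, which is 1 − (3 × 3)/15 = 2/5.
- Position 6: 1.

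The sum is 0.1 + 0.4 + 1 = 1.5 per block, and 1.5/6 = 25%. The general form for a block of 2m is a share of 1/(m + 1).

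**Guessing the arm with more places left.** The chance of a correct guess at positions 1 to 6 is 0.5, 0.6, 0.6, 0.7, 0.7 and 1.0. The sum is 4.1, and 4.1/6 = 68.3%, against 50% by chance.

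**Scaled to 116, all earlier allocations on the list known**
- One list, results shared between clinics: 116 = 19 × 6 + 2, so 19 × 1.5 = 28.5 certain (24.6%).
- One list per clinic, 58 and 58: each is 9 × 1.5 + 0.1 = 13.6, giving 27.2 (23.4%).
- One list per clinic, 69 and 47: 11 × 1.5 = 16.5, plus 7 × 1.5 + 0.1 + 0.4 = 11.0, giving 27.5 (23.7%).

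**One list across both clinics, staff seeing only their own clinic's results.** All three members of the exhausted arm must have been allocated at that clinic. With a share p there, the certain fraction is p³ × 0.25:
- p = 0.5: 0.125 × 0.25 = 3.1%.
- p = 0.6: 0.216 × 0.25 = 5.4%.

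A simulation gave the same two values.

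**Other fixed lengths.** From 1/(m + 1), a fixed block of 4 gives 33% and a fixed block of 8 gives 20%. A different fixed length therefore changes little. The useful step is to make the length variable and unknown to recruiters.

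**The case against.** The strongest objection is that the quarter is conditional. It needs someone who knows the block size and has followed the whole list, and the protocol does not show that any recruiter is in that position. With one list and knowledge limited to one clinic, the share falls to about 3% to 5%. This stands, and the size must be given as a range.

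Three stronger readings are tempting, and the protocol does not support them.
- A reader might infer that the list is not stratified by site. The text is silent. List structure may be set in a randomisation document that is not shown, and envelopes held by an independent statistician are compatible with central issue.
- A reader might infer that the same people recruit, allocate and assess. The protocol names research assistants as envelope openers, refers only to staff for care and outcome assessment, and does not say who approaches adolescents.
- A reader might infer that selection bias is built in. The schedule puts recruitment and baseline in month 3 and sessions in months 4 and 5. That is compatible with consent and baseline before allocation, though the order is not required.

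It is also fair to say that the outcomes are measured at baseline and that Table 2 adjusts depression for baseline. Adjustment would correct part of an imbalance in measured scores, but not selection on unmeasured motivation. The statistician's custody of the envelopes does not stop block counting.

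**Conclusion.** The point holds in conditional form. A single block length written into the protocol of an open-label trial, with numbered envelopes opened in order, makes up to about a quarter of allocations (about 27 to 29 of 116) knowable in advance and about 68% guessable. This applies to someone who knows the block size and all earlier allocations on that list. Under one shared list with own-clinic knowledge only, the certain share is about 3% to 5%, given 50% to 60% of participants at that clinic. The protocol does not settle which case applies.

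The weakness is avoidable, and cheap to remove before enrolment. Any selection that did occur could not be fully repaired in the analysis. For a study of feasibility and preliminary effectiveness, this is a worthwhile design improvement. It is not evidence that the results would be biased.

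**What to change.** Before enrolment:
- Replace the fixed block of six with computer-generated lists, one for Kisenyi and one for Kitebi, using randomly varying block sizes (for example 4, 6 and 8). Let only the independent statistician know the sizes, and keep them out of every document available to recruiting staff.
- State that each envelope is opened only after consent and baseline assessment are complete. This keeps knowledge of the opened assignment out of consent and baseline scoring. The varying blocks deal with anticipation before that point.
- Include site in the outcome model. The planned linear regression can carry it.

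The cost is a new list and a few lines of protocol text. The downside is a possible imbalance of a few participants per site. With a longest block of 8, an unfinished block can leave a difference of at most 4 at a site. Varying blocks do not remove guessing altogether, because the arm that is behind remains the better guess.

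### The fixed block size of six in an open-label trial leaves some allocations predictable if envelopes are opened during recruitment; one allocation after baseline would remove this

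*Protocol*

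**What the plan says.** The relevant statements are all in the protocol, under Sub-study Two.

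- The Randomization section sets one size: "A block size of six with equal individuals going to the two arms per block will be considered sufficient". The ratio is 1:1. No varying or withheld block size is described, and nothing is said about separate lists for the two sites.
- The Allocation concealment section places the sequence in numbered, opaque, sealed envelopes, which a statistician from outside the trial team holds.
- The use of those envelopes is described under Allocation implementation, as follows: "Trained research assistants will pick the envelopes in consecutive ascending order and allocate the participants to the different arms upon opening the envelope".
- On masking, the protocol declares the trial unblinded. Its reasons are that staff both give care and assess outcomes, and the kind of intervention under test.
- The Sampling method section says how adolescents are found: "convenience sampling will be used at the screening stage, adolescents will be approached for potential enrollment into the study".
- The sample-size section aims for "a total of 116 participants", that is 58 per arm.
- The Schedule of activities puts recruitment and baseline assessment in month 3. The first intervention sessions are in month 4, and standard care for controls is in months 4 and 5.

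**The concern.** With three places per arm in every block of six, anyone who counts the allocations already made knows the rest of the block once one arm's three places are used. In an open-label trial past allocations are not hidden. The envelopes stop someone reading the next allocation, but not inferring it. Convenience approach leaves staff free to decide whom to invite next, so foreknowledge could be acted on.

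The primary outcomes are questionnaire scores for depression, anxiety and internalized stigma, which can respond to motivation and expectation. If more promising adolescents were approached when an intervention place was expected, the arms would differ without any treatment effect. Adjustment for the baseline score would remove only the part of that difference which the score captures.

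**Working it through.** **The plan's own figure.** The sample-size inputs are a mean difference of 4.09, SD 5.13, and z values 1.96 and 0.84. Then 2 × 2.80² × 5.13² / 4.09² = 24.7 per group (stated as 25.1, taken as 26). Next, 26 × 2.0 = 52, and 52 / 0.90 = 57.8, so 58 per group and 116 in total. This reproduces closely enough. It is used here only for the number of allocations (116), the number analysed (52 per arm) and the planned effect, 4.09 / 5.13 = 0.80 SD.

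**Predictability when every earlier allocation is seen.** There are C(6,3) = 20 equally likely blocks. Enumerating them, the chance that an allocation is certain before opening is 0, 0, 0, 1/10, 2/5 and 1 at positions one to six. The sum is 1.5 of 6, or 25.0%. Guessing the arm with more places left, and at random when they are level, is right for 4.1 of 6, or 68.3%. Over 116 allocations there are 19 full blocks plus 2, so 19 × 1.5 = 28.5 are certain on average (24.6%). With a separate list of 58 per site (assumed split) it is 27.2 (23.4%).

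**Predictability under one list shared by both sites.** Assume that each place goes to either site with probability 1/2, and that staff know the serial numbers but see only their own site's allocations. Enumeration gives 3.1% certain and 58.4% guessed correctly.

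**Bias from steering.** Let staff shift the prognosis of the approached candidate by +δ or −δ SD according to the guess, with the guess right at rate g. The expected prognosis is then δ(2g − 1) in one arm and −δ(2g − 1) in the other. The difference under no effect is 2δ(2g − 1). The documents give no value for δ; 0.10 and 0.25 are assumptions. Type I error is for a two-sided 5% t-test with 52 per arm.

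| Case | g | δ | Difference (SD) | Type I error |
|---|---|---|---|---|
| All allocations seen | 0.683 | 0.10 | 0.073 | 6.6% |
| All allocations seen | 0.683 | 0.25 | 0.183 | 15.3% |
| Shared list, own site only | 0.584 | 0.10 | 0.034 | 5.3% |
| Shared list, own site only | 0.584 | 0.25 | 0.084 | 7.1% |

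The largest entry is 0.183 / 0.80 = 23% of the planned effect. Direct simulation of steering within blocks gave slightly lower error rates for the two all-seen rows, 6.1% and 14.0%. If the plan's design effect of 2.0 is carried into the test (effective 26 per arm), those rows give 5.8% and 9.9%.

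**Effect of varying the block size.** This was simulated over 116 allocations, for an observer who knows the possible sizes but not the realised ones.

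- Fixed six: 24.5% certain, 68.1% guessed.
- Random 4 and 6: 5.5% certain, 69.2% guessed.
- Random 4, 6 and 8: 2.3% certain, 67.9% guessed.

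**The case against.** A reader might infer that the plan as written makes a quarter of allocations certain and hands recruiters the means to steer. The text does not go that far. It does not say that those who approach adolescents open the envelopes or know the allocation history, that envelopes are opened at each enrolment, or that each site has its own list. The implementation section gives only the order of opening. That is compatible with opening after recruitment has closed, and the month-3 and month-4 timetable fits this reading too. On that reading recruiters have no foreknowledge. This objection stands, and it is why the figures are upper limits under stated conditions.

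A second objection also stands: the size of the bias rests on an assumed shift. It is driven by the guess rate, which varying the block size barely changes. The fixed block size accounts for the certain allocations, not for most of the guessing. If staff acted only on certain allocations, with a shift of 0.25 SD, the difference would be 2 × 0.25 × 0.25 = 0.125 SD and the type I error 9.7%.

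It can also be said that fixed blocks with sealed opaque envelopes held by an independent statistician are conventional, and that the trial claims only preliminary effectiveness. This limits the weight of the point. It does not answer it: custody of the envelopes does not prevent counting, and no separation of recruitment from allocation is described.

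**Conclusion.** The point holds in conditional form. A single disclosed block size, no masking, ordered opening by research assistants and discretionary approach together leave open a route to selection bias that concealment by envelope does not close. If envelopes are opened during recruitment, predictability ranges from about 3% certain and 58% guessed (shared list, own site visible, even split) to 25% certain and 68% guessed (all earlier allocations and block boundaries known).

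The documents do not show that steering would occur, so a type I error of 15% must not be read as a property of the design. It is the top of a range that requires full sight of allocations, a 0.25 SD shift for every candidate and 52 independent participants per arm. At 0.10 SD the error is close to nominal in either case. The change is still worth making, because the trial's own schedule makes the remedy nearly free.

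**What to change.** State that the independent statistician allocates the complete consented and baselined list 1:1 by computer in one step at the end of recruitment in month 3, and releases the allocations only then, before the month-4 sessions. Recruiters then know no allocation while they recruit. The cost is protocol wording and a wait of up to about four weeks for early recruits, longer if recruitment overruns. No extra participants or visits are needed.

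If sequential envelopes are kept:

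- Use randomly varying block sizes that are not disclosed to recruiting staff.
- Record participant ID and date on each envelope before it is opened.
- State who recruits, who opens the envelopes and when, and whether the sites share a list.

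This removes most of the certain allocations but hardly lowers the guessing rate, so it is the weaker option.

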#### *Allocation concealment*

The sequence will be concealed using sealed serialized brown opaque envelopes that will be kept by the independent statistician who is not part of the study.

#### *Allocation implementation*

Trained research assistants will pick the envelopes in consecutive ascending order and allocate the participants to the different arms upon opening the envelope.

#### *Blinding:*

This will be an open-label randomized study because the staff will be involved in the care of the participants, assessment of the outcome and the nature of the psychosocial interventions to be administered.

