### Study instruments

*Beck's Depression Inventory ii (BDI ii, Beck et.al, 2006)*. BDI-ii is a 21 item self-report rating inventory widely used to measure the presence and degree of depression among adolescents and adults. The BDI-ii includes both cognitive and somatic symptoms of depression. It has a high test retest reliability  $r=.93$  and high internal consistency  $\alpha=.91$ . In scoring the BDI-ii, each of the 21 items is summed up to give a single score. Each item has a 4-point scale ranging from 0-3, except items 16&18 that have 7 options indicating either an increase or decrease of appetite and sleep. The total score in the range of 0-13 =minimal range, 14-19=mild, 20-28=moderate and 29-63= severe.. The cut-off guidelines for BDI-ii are adjusted basing on characteristics of the sample.

*Avoidance and Fusion Questionnaire for youths (AFQ-Y8; Greco et.al, 2008)*. This is a measure of psychological inflexibility among children and adolescents. It is an 8-item instrument where participants rate their level of agreement with statements targeting cognitive fusion and experiential avoidance such as "my thoughts and feelings mess up my life". AFQ-Y8 is scored on a 5-point Likert scale made up of a single factor. Scores range from 0-24, with higher scores indicating higher levels of psychological inflexibility. The instrument has shown excellent internal

consistency ( $\alpha=.90$ , and test-retest validity  $r=.80$ ). It also correlates well with measures of anxiety, depression and anger and is better recommended for use among adolescents.

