## Study intervention

### ACT-DNA-v

Uses language, metaphors, mindfulness and experiential learning to encourage young people to defuse distressing psychological experiences and adopt an accepting stance towards one's experience as it unfolds in real-time while pursuing behavioral goals derived from personal life value. This enables them to engage in value-led behaviors such as medication adherence.

The intervention involves four sessions delivered in six weeks, with each session lasting two hours a week, for a total of 12 hours. The sessions will be delivered by HCPs (counsellors) together with the research team. All four sessions strengthen the appropriate use of discover, noticer and advisor skills in line with values to improve psychological flexibility.

Table 1; showing sessions of the ACT-DNA-v

|           |                                                                                                |
|-----------|------------------------------------------------------------------------------------------------|
| Session 1 | About DNA-V, being yourself, using social DNA to build groups, the challenge of choosing       |
| Session 2 | The Noticer: normalizing noticer, practice awareness, noticer sessions, responding to signals  |
| Session 3 | The Advisor: normalizing adviser, helpfulness of advisor, games to unhook from advisor         |
| Session 4 | Discoverer: meeting your discoverer, build strength, try it-track it-build it, DNA-V in action |
| Session 5 | Values: small things matter, introduction of values, value is success                          |
| Session 6 | Who you are, making yourself, ways of well-being, social DNA, and closure.                     |

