#### Outcome measures.

Measured clinical primary outcomes will include Experiences of depression, anxiety and internalized stigma. Then process outcomes will include; Psychological flexibility (cognitive fusion and experiential avoidance) to test the mechanism of change and secondary outcomes will be; self-reported adherence and viral load (obtained from clinical charts).

Table 2; Showing study measures, analysis and outcomes.

| Objective                                                             | Variables                                                                                                                                      | Informant | Measures                                                                                                                                                                                                                                                                                                                                                                                                                                                      | Analysis & Outcomes                                                                                                                                                                                                                                                                                                                                                                             |

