| To measure the effectiveness of a mindfulness-based intervention (ACT-DNA-v) on psychological flexibility among ALWHA in Kampala.                  | Process variable:
*Psychological flexibility. | ALWHA | Qualitative surveys using standardized self-administered instruments

* Avoidance and Fusion Questionnaire for youths (AFQ-Y8).                                                                                                          | 
Analysis
We shall run a T-test, linear regression, and Fisher's exact and Chi-square tests respectively to obtain mean differences between groups.
 
Outcomes
*The average mean scores of participants in the intervention group will be above the cut-off score on psychological inflexibility using the AFQ-8 at post-intervention and follow-up adjusting for baseline scores.
                                                                                                                                                                                                                                                                                                                                                                                                                       |

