## Intervention fidelity

To ensure that delivery of the intervention adheres to the underlying theoretical premises and the protocol, sessions will be audiotaped and reviewed by two independent raters (ACT experts) to determine if all critical components are delivered. The aim will be to achieve a fidelity rating of at least 85% for all sessions.

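### Staff who care for participants also assess the outcomes, and the protocol does not say that the self-reported primary scales are completed in private, away from those who led the sessions

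*Protocol*

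**What the plan says.** The Blinding section explains that the trial is open label because "the staff will be involved in the care of the participants, assessment of the outcome and the nature of the psychosocial interventions" to be used make masking impractical. Care and outcome assessment thus fall to the same staff, and that overlap is offered as a reason for not blinding. On delivery, the ACT-DNA-v section says: "The sessions will be delivered by HCPs (counsellors) together with the research team".

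On the endpoints, the Outcome measures section says: "Measured clinical primary outcomes will include Experiences of depression, anxiety and internalized stigma". Viral load, the only outcome that does not depend on participants' own answers, is secondary.

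On how the scales are completed, the text is uneven. Study instruments states that "BDI-ii is a 21 item self-report rating inventory". Table 2 describes the AFQ-Y8, the process measure, under "Qualitative surveys using standardized self-administered instruments". The Table 2 row for the three primary outcomes refers to standardized instruments without saying who completes them. Data collection and measures does not say who administers the scales, where, or who is present.

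The comparator is active contact of a kind: "the control group will receive standard of care (ART related counselling").

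**The concern.** A talking therapy cannot be masked from those who give or receive it. It does not follow that the people who give it must be present when its effect is measured. The protocol presents the second as part of the first.

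The three primary outcomes ask adolescents about their mood, health worries and shame about HIV. An adolescent who completes these scales in front of a counsellor or team member who led the groups may report improvement partly to please that person. The ACT-DNA-v section counts 12 hours of session time in total, and Strategies for retaining participants adds refreshments and a transport refund at each session. That contact belongs to the intervention programme, so any such effect would tend to favour it.

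A shift of this kind is a bias. More participants would not remove it and would make it more likely to be declared significant. The stake is the use of the result: under Utility of findings, the trial is meant to support adding the approach to routine psychosocial services.

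**Working it through.** This is mainly a matter of reading the sections together.

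1. **Who assesses.** Blinding: staff involved in care. No section provides an assessor independent of care or of session delivery.
2. **Who delivers.** ACT-DNA-v: counsellors with the research team. The people in step 1 may therefore include session leaders.
3. **What is assessed.** Outcome measures and Study instruments: three subjective primary outcomes. The participant answers and staff do not rate. The risk is favourable answering near treating staff.
4. **How the scales are completed.** Self-report is stated for the BDI-II and self-administration for the AFQ-Y8. Privacy is stated for no scale in particular. Confidentiality and Privacy asks only for settings that are as private as possible and does not exclude session leaders. Consent procedure and documentation plans for forms read aloud and thumbprints for those who cannot write, so some participants may need help with the scales too.
5. **Where independence is already used.** An independent statistician keeps the sequence (Allocation concealment), and recordings are "reviewed by two independent raters (ACT experts") for fidelity. Nothing similar is assigned to the outcomes.
6. **Contact in each arm.** Controls receive ART counselling, and the inclusion criteria require attendance at the clinics for the last 6 months. Both arms know clinic staff. What differs is the session contact.

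**The plan's own figure.** Sample size section, with Z values 1.96 and 0.84, SD 5.13 and difference 4.09:

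- N = 2 × (1.96 + 0.84)² × 5.13² / 4.09² = 2 × 7.84 × 26.3169 / 16.7281 = 24.7 per arm. The protocol prints 25.1 and uses 26, a negligible difference.
- 26 × 2.0 (design effect) = 52; 52 / 0.90 = 57.8, so 58 per arm and 116 in total. This is reproduced, and nothing in this point changes it.

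**Illustration of scale (assumption, not an estimate).** The documents give no figure for reporting bias. Let b be a net between-arm reporting shift in SD units, with no true effect. The standard error is √(2/n), and the two-sided rejection rate is Φ(b/SE − 1.96) + Φ(−b/SE − 1.96). The effective n per arm is 26 (52 completers with design effect 2.0) or 52 (no clustering).

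| b (assumed) | n = 26, SE 0.277 | n = 52, SE 0.196 |
|---|---|---|
| 0 | 5.0% | 5.0% |
| 0.1 | 6.5% | 8.0% |
| 0.2 | 11.1% | 17.5% |
| 0.3 | 19.1% | 33.4% |

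For example, at b = 0.2 and n = 26: b/SE = 0.721, and Φ(−1.239) + Φ(−2.681) = 0.108 + 0.004 = 0.111.

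On the planning figures, 0.1 to 0.2 SD is 0.51 to 1.03 points (0.1 × 5.13 and 0.2 × 5.13), or 13% to 25% of 4.09. Those points are on the RADS-2 of the cited study and do not carry over to the BDI-II, SHAI or IARSS. The table is in SD units and does not depend on the instrument.

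**The case against.** **The mode of completion may already be self-completion.** The BDI-II is called self-report, and the SHAI rule for more than one selected statement fits a form that the respondent marks. Assessment by staff may mean only handing out forms. This stands in part: it rules out a claim of biased rating by unblinded staff, which a reader might infer from the Blinding section. It does not settle who is in the room or who reads the items aloud.

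**The effect is not confined to one arm.** A reader might infer that only intervention participants have a relationship with the assessors. The documents do not support that, because controls are counselled at the same clinics and have attended for at least 6 months. What remains is a difference in degree, arising from the sessions.

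**The available staff are not known to be free of delivery.** A reader might infer that the existing research assistants could take over assessment, for instance by changing sites. The protocol says only this of them: "Trained research assistants will pick the envelopes in consecutive ascending order". Their number and sites are not given, they learn the allocation, and the research team that helps deliver sessions could include them. This objection stands, so the remedy should not depend on them.

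**The main bias would remain.** Participants know whether they attended the sessions, and that expectation cannot be removed against standard care. This is true; only the part due to staff presence is avoidable.

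**This is operational detail in a preliminary trial.** Who hands out forms is often left to a manual, and the protocol calls the effectiveness aim preliminary. But the protocol does not leave the matter open: it assigns assessment to staff involved in care.

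**Conclusion.** The point holds in a limited form. As written, the protocol lets people who care for participants, and may have led their sessions, be present at or assist with three subjective primary outcomes, and it states the mode of completion unevenly. A shift favouring the intervention is plausible because only that arm has the added session contact.

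The size cannot be estimated from the documents. The illustration rests on an assumed shift, no true effect, a normal approximation and the protocol's own design effect. It shows that a modest shift would matter, not that one will occur.

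This is an avoidable weakness that is cheap to reduce. It does not invalidate the trial, and removing it would not make the comparison free of reporting bias.

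**What to change.** Amend Blinding and Data collection and measures, before baseline assessment, to state that:

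- the BDI-II, SHAI, IARSS and AFQ-Y8 are self-completed in private, in the same way in both arms and at every assessment;
- nobody who delivered sessions is present;
- any reading help comes from a team member who did not deliver sessions to that participant and, where the roster allows, did not open that participant's envelope.

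Blinding should also stop giving the overlap of care and outcome assessment as a reason for the open-label design; the nature of the intervention is reason enough. The protocol should acknowledge as a limitation that participants' knowledge of their own arm can still influence their answers.

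The cost is some rostering on assessment days and a check of who delivered which sessions. Sample size, outcomes and analysis do not change.
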